### Other measures

Characteristics of the parents/caregivers including age, gender, country of birth, educational level, employment situation and marital status are collected. Perceived social support, general happiness, general health and psychological distress are also assessed. Social support perceived by parents/caregivers will be measured using the Multidimensional Scale of Perceived Social Support (MSPSS) [35, 36]. Happiness will be measured with a single item “Do you feel happy in general” on an 11-point scale [37]. General health will be measured using the first item of the short form 12 (SF-12) health survey [38]. Psychological distress will be measured using the Brief Symptom Inventory 18 (BSI-18) [39]. The BSI-18 includes three subscales: depression, anxiety, and somatization. Additionally, the global severity index will be computed as an overall general psychological distress score. One item (thoughts of ending your life) will not be assessed in this study, due to possible invasiveness to the parent/caregiver.

Characteristics of the child include gender, age, country of birth, birth weight, gestational age at birth, pregnancy and birth complications, general health (assessed with the first item of the Child Health Questionnaire [40], use of child daycare service, medicine use for problems regarding social and emotional development and diagnoses of physical and mental disabilities.

Characteristics of the family include household income, family compositions, country of birth of grandparents and the occurrence of 12 stressful life events within the previous year (moving to another address; a friend of the child moving to another address; tension at the parents’ work that has been felt at home; financial problems; rows with neighbors, friends, acquaintances or family; fire or burglary; problems with the physical health of people in close proximity; problems with the psychological health of people in close proximity; death of someone in close proximity; problems in the marriage relation; divorce and unemployment). If an event occurred, the perceived severity of the stress or tensions in the family caused by the event was additionally assessed.

### Received parenting support and use of care

In the baseline questionnaire, the use of various types of care in the previous year by the parent/caregiver, child and/or other children in the family will be assessed, including the general practitioner, medical specialists, psychological help, parenting support and other types of care (18 items). Furthermore, we include 3 items regarding visits to the youth health care centers.

In the follow-up measurement, the use of care will be assessed similarly as in the baseline questionnaire. Additionally, 3 items are included to assess whether parents/caregivers had questions or concerns regarding the upbringing of their child, whether they had been in need for parenting support and whether they have received parenting support during the follow-up period. Visits to youth health care centers, participation in parenting interventions, visits to parenting lectures and other types of parenting support during the last year are assessed by 20 items, including items considering the duration, frequency, character, content and the parents’/caregivers’ appreciation of the received parenting support. Additionally, when available and with permission of participants, data on received parenting support and care regarding parenting during the follow-up period will be collected from electronic files of preventive youth health care organizations.

### Elements in parenting interventions and other types of support

Elements of the parenting support that were received by parents/caregivers will be identified and coded. For this purpose, we will inventory the guidelines and/or protocols of the interventions that were reported by the parents/caregivers. In this study, content elements (objectives or general themes/principles) and delivery elements are extracted [12]. Delivery elements are operationalized as elements related to what was delivered in the intervention (i.e. the ‘active ingredients to change behavior’ or behavior change techniques) and how the intervention was delivered (i.e. who delivered, to whom, how often, for how long, in what format, and in what context). Behavior change techniques were categorized using the taxonomy of Michie [12]. This taxonomy includes 93 Behavior Change Techniques, grouped into 16 categories; for example the categories feedback and monitoring, comparison of behavior, repetition and substitution. Moreover, contextual (e.g. characteristics of target participants who receive the interventions) characteristics of the parenting interventions will also be assessed.

### Data management and statistical analysis

Data are handled according to the guidelines of the EU General Data Protection Regulation (GDPR). Data-management and analysis will be carried out at the Erasmus MC University Medical Center. Paper questionnaires will be transferred into electronic files and checked for missing or incorrect data. All data are handled confidentially and scientific data are stored anonymously.

Descriptive statistics will be used to describe the characteristics of the study population. We will use linear regression analysis for continuous outcome measures, and logistic regression analysis for dichotomous outcome variables. The exposure to (elements of) parenting interventions (yes/no) is the independent variable. In additional models, the baseline measurements and potential confounders (e.g. demographic characteristics of the caregivers and children) will be added. It will be evaluated whether additional multi-level regression analyses should be performed given the potential clustering within the youth health care organizations in the study. The exposure to parenting support will be based on information obtained from the follow-up questionnaire and when available the electronic files of the youth health care organizations. All analyses will be performed using SPSS version 24 for windows and R (version 3.4.1). Missing data will be handled by multiple imputation. All tests will be two-sided and *p*-values less than 0.05 will be considered as significant.

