## Methods/Design

### Preventive youth health care in the Netherlands

The preventive youth health care is a system for monitoring children’s health and development, and for providing health promotion and disease prevention [21]. It is offered nation-wide and free of charge, independent of insurance status. Participation is voluntary. From birth onwards, parents are frequently invited with their child to visit preventive youth health care centers. The attendance rate is about 95%. During these visits, the growth, development, health and well-being of the child are assessed [21–23]. Additionally, youth health care professionals provide information about the development and upbringing of children and promote a stimulating pedagogical climate. They aim to identify child behavior problems or parenting problems in an early stage and organize help when needed. The youth health care professionals can provide pedagogical counseling or they can direct parents and families to parenting interventions offered by themselves or other providers [1, 24]. In this way, youth health care providers can serve as link with specialized services; they are the frontline services for a broad range of questions [24]. Municipalities are responsible for the preventive youth health care and facilitate a suitable offer of preventive services and coordinate the collaboration between these services [1, 24].

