### Study design

The design is a naturalistic effect evaluation [19]. It is an observational prospective cohort study with a baseline and follow-up measurement (12 months after inclusion). The total study sample will consist of parents with various levels of parenting problems and concerns. Both at baseline and at follow-up, all participating parents/caregivers will be asked to complete a questionnaire. There are no separate intervention and control groups in this study. The exposure of parents/caregivers to (elements of) parenting support during the follow-up period will be established by the follow-up questionnaire and from electronic files of the youth health care organizations (only with permission by the study participants, see below). By comparing the outcome measures between baseline and follow-up measurements, we aim to investigate which interventions and/or elements of parenting support are associated with a relative decrease in problems and improvement in positive outcome measures in parents and their children.

Data collection started in October 2017 and will continue until April 2020.

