Parents’/caregivers’ satisfaction with parenting and their self-efficacy in the parenting role will be assessed with the Parenting Sense of Competence Scale (PSOC) [31]. The PSOC contains 17 items with two subscales: satisfaction and efficacy. Parents indicate their agreement with a series of statements regarding degree of confidence and satisfaction in carrying out their parenting role on a 6-point Likert scale (1 = strongly agree, 6 = strongly disagree). Higher scores indicate higher levels of parenting self-efficacy and satisfaction.

Family stress will be assessed by the seventh subscale (General Functioning) of the Family Assessment Device (FAD) [32, 33]. The FAD is a self-report measure of family functioning. The General Functioning scale consists of 12 items about support and stress within the family, providing a measure of overall health/pathology of the family. Each item receives a score from 1 (strongly agree) to 4 (strongly disagree), with the scale for the negatively worded items reversed. The sum of values is divided by 12 to give a total score ranging from 1 to 4. Higher scores indicate poorer family functioning.

Children’s emotional and behavioral problems will be assessed using the Child Behavior Check List (CBCL/1,5–5) [34]. The CBCL contains 99 items concerning the child’s behavior in the previous 2 months. Each item is scored on a three-point scale with 0 (not true), 1 (somewhat or sometimes true) and 2 (very true or often true). The CBCL includes seven empirically-based syndrome scales: emotionally reactive, anxious/depressed, somatic complaints, withdrawn, sleep problems, attention problems, and aggressive behavior. Two broad band scales can be derived. An internalizing problem score can be derived by summing the subscales emotionally reactive, anxious/depressed, somatic complains, and withdrawn and an externalizing problem score can be derived by summing the subscales attention problems and aggressive behavior scales. A total problem score can be computed by summing all 99 items. Additionally, there are five scales oriented at the Diagnostic and Statistical Manual for Mental Disorders (DSM); affective problems, anxiety problems, pervasive developmental problems, attention deficit/hyperactive problems, and oppositional defiant problems. Higher scores indicate higher levels of emotional and behavioral problems.

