### Power considerations

In total, we aim to include net 1000 parents/caregivers in the study. With an expected 40% loss to drop-out between baseline and follow-up, we expect complete data of *n* = 600 participants. We assume that 50% (300) of these parents/caregivers will have received parenting support during the follow-up period. We assume an alpha of 0.05 (2-tailed) and power of 0.80. We apply a correction factor to account for the cluster design, assuming 25 clusters within the sample with an average cluster size of 24 participants and an intra-class correlation coefficient of 0.02. For this expected sample size and assumptions, with regard to the continuous outcome measures, a difference of 0.27 SD (standard deviation) between the subgroup exposed to parenting support and the subgroup not exposed to parenting support can be detected at follow-up. This is enough to indicate relevant effects, as a difference of 0.5 SD is considered meaningful [41, 42].

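### Linear regression with its default standard error could be too liberal for rarely used interventions or elements on floor-bounded problem scores; robust standard errors would largely cure it

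*Protocol article*

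**What the plan says.** The section Data management and statistical analysis sets the model: "We will use linear regression analysis for continuous outcome measures". It sets the contrast: "The exposure to (elements of) parenting interventions (yes/no) is the independent variable". Adjustment comes in a second step: "In additional models, the baseline measurements and potential confounders (e.g. demographic characteristics of the caregivers and children) will be added". Tests are two-sided at 0.05, in SPSS and R, with multiple imputation. The section raises one departure from simple errors, namely clustering within youth health care organisations, for which multi-level models will be considered. It does not mention unequal variance.

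The outcomes include sums with a floor at zero. For the CBCL, whose items are scored 0 to 2, Outcome measures says: "A total problem score can be computed by summing all 99 items".

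On who is studied and who receives support, Study design says: "The total study sample will consist of parents with various levels of parenting problems and concerns". The section on preventive youth health care says of its professionals: "They aim to identify child behavior problems or parenting problems in an early stage and organize help when needed".

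**The concern.** Default least-squares inference uses one residual variance for all families. That is harmless when the two groups are of equal size or have equal spread. It fails when the smaller group has the larger spread, because the pooled variance then reflects the large group while the uncertainty of the contrast comes mainly from the small one.

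The article makes this pattern plausible for some contrasts. Most of the sample (net 800 of 1000) is invited from general registries, so many problem scores should lie near the floor. Help is organised partly according to need. The exposed are also divided over many interventions: 19 are relevant to this population, and 93 behaviour change techniques may be coded. Adding the baseline score as a covariate removes a difference in mean but not a difference in variance.

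At stake are the intervals and p-values for single interventions and uncommon elements, which are central to the study's purpose. A residual check on the balanced contrast of any support against none would not reveal the problem.

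**Working it through.** **1. The plan's own figure.** Power considerations gives 600 completers, 300 exposed, 25 clusters of 24, ICC 0.02, and "We assume an alpha of 0.05 (2-tailed) and power of 0.80".
- Design effect = 1 + (24 − 1) × 0.02 = 1.46.
- Detectable difference = (1.960 + 0.842) × √(2 × 1.46 / 300) = 0.276 SD.
- Power at 0.27 SD is 78.1%.

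The stated 0.27 SD is therefore reproduced to within two points of power. It uses one common SD and an equal split, so it says nothing about small exposed groups.

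**2. How small could the groups be?** The article gives no count per intervention or element. If each of the 300 exposed completers used exactly one of the 19 interventions, the average would be 300 / 19 ≈ 16. Part B's net 200, after the assumed 40% loss, is 120. Exposed counts of 16 to 120 are used below as assumptions.

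**3. Large-sample size of the pooled-variance test.** Let r be the SD in the exposed divided by the SD in the unexposed (assumed), n1 the number exposed and n0 = 600 − n1.
- Variance used by the test: s² (1/n1 + 1/n0), with s² = [(n1 − 1) r² + (n0 − 1)] / 598.
- True variance: r²/n1 + 1/n0.
- Actual size = 2 × [1 − Φ(1.96 × √(used / true))].

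Example with n1 = 30, r = 1.5:
- s² = (29 × 2.25 + 569) / 598 = 1.061
- used = 1.061 × 0.03509 = 0.0372
- true = 0.0750 + 0.0018 = 0.0768
- √(0.0372 / 0.0768) = 0.696, and 1.96 × 0.696 = 1.365, giving a size of 17.2%

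| Exposed of 600 | r = 1.2 | r = 1.3 | r = 1.5 |
|---|---|---|---|
| 15 | 9.9% | 12.7% | 18.2% |
| 30 | 9.6% | 12.1% | 17.2% |
| 60 | 9.0% | 11.2% | 15.4% |
| 120 | 7.9% | 9.3% | 12.1% |
| 200 | 6.5% | 7.2% | 8.5% |
| 300 | 5.0% | 5.0% | 5.0% |
| 480 | 2.9% | – | 1.3% |

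**4. Simulation with baseline adjustment.** The formula ignores the baseline covariate, so the planned adjusted model was simulated: 600 families, no exposure effect, 3,000 runs per setting. The score is a skewed count with a floor at 0 (assumed mean 20, between-family coefficient of variation 0.8, within-family variance 1.5 times the mean). The log-odds of exposure rise by 0, 0.5 or 1.0 per baseline SD. Follow-up is regressed on exposure and baseline.

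| Exposed | Selection on baseline | Residual SD ratio | Default | HC3 |
|---|---|---|---|---|
| 30 | none | 0.97 | 5.3% | 5.2% |
| 30 | 0.5 | 1.21 | 10.3% | 5.2% |
| 30 | 1.0 | 1.47 | 14.4% | 5.2% |
| 60 | 0.5 | 1.22 | 9.8% | 6.0% |
| 60 | 1.0 | 1.42 | 11.6% | 5.4% |
| 120 | 0.5 | 1.21 | 7.8% | 5.3% |
| 120 | 1.0 | 1.39 | 8.7% | 5.4% |
| 300 | 0.5 | 1.19 | 4.7% | 5.2% |
| 300 | 1.0 | 1.35 | 4.3% | 5.5% |

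Without selection on baseline the default test holds its level. HC3 restores it under selection, so the excess comes from the standard error and not from a biased estimate.

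**5. Sensitivity to the assumptions.** A second model used a negative-binomial baseline (mean 8, k 1.2) and follow-up (mean 3.2 + 0.6 × baseline, k 2).
- Exposed about 0.6 SD higher at baseline: 13.8%, 11.8%, 10.0% and 8.6% with 16, 30, 60 and 120 exposed. HC3 gave 7.0%, 5.5%, 5.1% and 5.4%.
- Exposed about 0.2 SD higher: 8%, 7% and 6% with 30, 60 and 120 exposed.
- A higher, less dispersed score (mean 30, k 2.5 and 6): 6 to 10% with 60 exposed.

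**The case against.** The strongest reply is that the article states nothing false. It says linear regression and does not mention constant variance, and robust standard errors are fully compatible with its sentence. The type of standard error is also something an article commonly leaves to the full protocol or analysis plan. This stands in part: the article cannot be charged with choosing a constant-variance analysis. But it does fix the model, the exposure term, the software and the significance level, and it names clustering as the only departure to consider. A multi-level model with a single residual variance would not correct unequal spread. A reader who follows the text with default settings gets the result above.

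A reader might also infer that the study's 5% test in fact runs at 10 to 17%. The documents do not support that. They give no SD, variance ratio, baseline difference or exposed count for any intervention or element, and the only stated split shows no inflation. Nor is the effect shown for every outcome or exposure. The PSOC is not a problem score, and the article does not say that the hassle ratings are summed. Elements are coded from manuals and may be shared by many interventions, so their exposed groups may be large. Informal support and routine monitoring visits also count as support and are not aimed at families with high scores.

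**Conclusion.** The point holds conditionally. With the default standard error, tests and intervals could be too liberal for contrasts with few exposed families on floor-bounded problem scores such as the CBCL. With 16 to 60 exposed of 600, and exposed families about 0.25 to 1.0 SD higher at baseline or a residual SD ratio of 1.2 to 1.5, the nominal 5% test could run at about 6 to 17%. With about 120 exposed, the adjusted simulations give about 5 to 9%; the formula without the covariate reaches 12% at a ratio of 1.5. At 300 against 300 there is no inflation and the test is slightly conservative. When more than half are exposed, it is conservative.

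The exposed counts, baseline shift, SD ratio and score distributions are all assumptions. Clustering and confounding are separate matters not covered by these figures.

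**What to change.** Add one sentence to Data management and statistical analysis: linear models report heteroscedasticity-consistent (HC3) standard errors, or cluster-robust ones where clustering is handled, computed within each imputed dataset and then pooled. Reporting the number exposed beside each estimate would let readers see where the issue could matter.

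This needs no new data and leaves the point estimates of the linear regressions unchanged. Intervals become slightly wider. Because the plan combines imputation with possible multi-level models, it takes some programming rather than a single switch; R is already among the listed software. HC3 is not a complete cure: with very few exposed it stays mildly liberal, at about 6 to 8%, so such contrasts should be read with caution.

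A negative-binomial model for the problem sums is an optional check only, because it changes the effect from a difference in means to a ratio.

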**Methods/design:**

Thousand parents/caregivers are recruited by preventive youth health care providers in the Netherlands. Measurements will be performed after inclusion and after 12-months follow up. Data regarding child/parent/caregiver characteristics, use of (parenting) interventions and care, and outcomes with regard to parenting skills, family functioning and child development will be collected. Outcomes will be compared between parents/children exposed and non-exposed to the (elements of) parenting interventions (adjusting for confounders).

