To study the exposure of parents to (elements of) parenting interventions and other types of parenting support in the daily practice of the preventive youth health care.To investigate the associations between the exposure to (elements of) parenting interventions and other types of parenting support and outcomes in parents and children related to parenting and child development (see below).

The hypothesis is that parents/caregivers who receive (elements of) parenting support during the follow-up period will show (relatively more) improvements in parenting skills, family functioning and child development compared to comparable parents/children who did not receive parenting interventions.

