The proposed study also has some limitations and we expect to encounter some challenges. The first challenge of this study will be to include parents at risk of parenting problems. It may be a difficult group to reach, and these parents may be hesitant to participate in research [44]. To increase participation, we will recruit these parents through providers of parenting support. Second, because of the non-randomized design, results of the study are subject to confounding variables. We will assess the most important confounding variables; however, there may be residual confounding. Another limitation is that it is not possible to evaluate some general elements that have been shown to be of importance to the effectiveness of parenting interventions in our study design, such as the quality of the implementation of the interventions [7]. Although we cannot include it in our study, we know that these factors may be important to take into account and we emphasize the need to investigate these factors more thoroughly in future studies.

In conclusion, results of the naturalistic effect evaluation study will provide insight in which parenting support elements and strategies are used in daily practice, and which elements are effective. The results will be translated into products for practice and education; recommendations for practice and policy will also be made. The knowledge provided by CIKEO is valuable for various stakeholders in practice, including providers of parenting support (youth health care organizations and parent training institutes) and municipalities that provide interventions. It will enable professionals and policy makers to concentrate on elements of parenting support that are shown to be effective and to adapt parenting support to better fit the needs of clients and the possibilities within organizations and local settings. Furthermore, it may guide the future development and improvement of interventions. Ultimately, the goal is to make parenting support more flexible and more effective.

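### The element-level contrast compares supported parents with mostly or wholly unsupported ones, so an element's coefficient also carries the rest of the intervention and selection into support

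*Protocol article*

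**What the plan says.** In Data management and statistical analysis, one sentence defines the exposure for whole interventions and for elements together: "The exposure to (elements of) parenting interventions (yes/no) is the independent variable". The next sentence adds baseline measurements and potential confounders in additional models, with demographic characteristics as the example.

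The comparator appears in two forms. The abstract (Methods/design) has "Outcomes will be compared between parents/children exposed and non-exposed to the (elements of) parenting interventions (adjusting for confounders"). The hypothesis at the end of the Background has supported parents "compared to comparable parents/children who did not receive parenting interventions", and the Discussion repeats this for parents exposed to elements. Groups are formed afterwards from reported exposure: "There are no separate intervention and control groups in this study" (Study design).

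To code elements, "we will inventory the guidelines and/or protocols of the interventions that were reported by the parents/caregivers" (Elements in parenting interventions and other types of support). Power considerations gives the expected split: "We assume that 50% (300) of these parents/caregivers will have received parenting support during the follow-up period". The Discussion says the results will show "which parenting support elements and strategies are used in daily practice, and which elements are effective". The article names no comparison, among supported parents, of those with an element and those without it.

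**The concern.** Whether support helps and whether a particular element helps are different questions and need different reference groups. Parents exposed to an element also received everything else in the same intervention, and they differ from unsupported parents in whatever led them to support. Part B sharpens the selection issue, because its net 200 families are recruited on the ground that they will take part in an intervention.

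If the reference group is mostly or wholly unsupported, an element that does nothing still picks up a large part of the supported-versus-unsupported difference. That difference may be favourable (effect of the other components) or unfavourable (families with more problems seek support). Identifying effective elements is the consortium's overarching aim, and the Discussion intends the results to guide practice, policy and new interventions.

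**Working it through.** **Inputs from Power considerations.** 600 analysed parents, 300 supported and 300 not; two-sided alpha 0.05; power 0.80; average cluster size 24; intra-class correlation 0.02.

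**Assumptions not in the article.** The share p of the cohort that received a given element (10% to 40%). The supported-versus-unsupported difference d, set at 0.27 SD only because that is the plan's detectable difference; the plan does not call it an expected effect.

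**Step 1: the plan's own figure.** Design effect = 1 + (24 − 1) × 0.02 = 1.46. Detectable difference = (1.960 + 0.842) × √(2 × 1.46 / 300) = 0.276 SD, which agrees with the stated 0.27 SD apart from rounding (power at exactly 0.27 SD is 0.78). It is calculated for any support (300) against none (300), not for an element.

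**Step 2: reference group = all element-unexposed parents (abstract).** The 600p exposed parents are all supported. Of the 600(1 − p) unexposed, 300 are unsupported, a share of 300 / [600(1 − p)] = 0.5 / (1 − p). An inert element has expected coefficient d × 0.5 / (1 − p). Its standard error is √[1.46 × (1/n₁ + 1/n₀)], with n₁ exposed and n₀ unexposed; the last column uses a normal approximation.

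| p | exposed / unexposed | unsupported share of unexposed | coefficient of inert element (d = 0.27) | chance of p-value < 0.05 |
|---|---|---|---|---|
| 10% | 60 / 540 | 56% | 0.15 SD | 15% |
| 20% | 120 / 480 | 63% | 0.17 SD | 28% |
| 30% | 180 / 420 | 71% | 0.19 SD | 43% |
| 40% | 240 / 360 | 83% | 0.23 SD | 61% |

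**Step 3: reference group = parents with no intervention (Background, Discussion).** If these are the unsupported half, the inert element inherits all of d, here 0.27 SD.

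**Step 4: selection alone.** Suppose support has no effect and supported parents score 0.3 SD worse (an assumption). In a simulation with 300 supported and 300 unsupported parents, no clustering and no adjustment, an inert element received by 25%, 50% or 75% of supported parents showed −0.17, −0.20 and −0.24 SD. It was significant in 27%, 56% and 82% of runs.

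**Step 5: with an any-support indicator added.** In the same simulation, and in runs with d = 0.27 or 0.5 SD, the inert element's coefficient was about 0 and it was significant in 4.6% to 5.7% of runs.

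**Step 6: precision among the 300 supported parents.** Detectable difference = 2.8016 × √[1.46 × (1/n₁ + 1/n₂)], with n₁ and n₂ the supported parents with and without the element:
- 150/150: 0.39 SD
- 90/210: 0.43 SD
- 60/240: 0.49 SD
- 30/270: 0.65 SD

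With 12 supported parents per cluster the design effect is 1 + 11 × 0.02 = 1.22, and the two extremes become 0.36 and 0.60 SD.

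**The case against.** The strongest reply is that the exposure sentence is condensed, that adjusted models follow it, and that the confounder list is open, so an unseen analysis plan could add an any-support term. The article also concedes residual confounding. Part of this stands: it would be wrong to read the plan as a one-regressor analysis, and adjustment for baseline scores may well reduce the selection part. But the rest of the intervention is delivered during follow-up. It is not a baseline characteristic, and neither baseline scores nor demographics can remove its effect. The article does more than leave detail open: it names the exposure and the comparator, and on both readings of the comparator the element is confounded with receipt of support. The general concession on residual confounding does not address this.

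Other stronger readings are tempting but unsupported:
- A reader might infer that books, websites and consultations will be counted as element-unexposed because they have no manual. The article does not say so. It plans to code elements of the support received, and the follow-up questionnaire records its content.
- A reader might infer that every element is fixed by the intervention received. That fits techniques read from the manual, but duration and frequency are recorded per parent and can vary within an intervention.
- A reader might take the comparison group to have had no support of any kind. The article also studies informal sources and routine monitoring visits, and attendance at youth health care is about 95%. The 50% therefore implies a narrower definition of support, which is not stated.

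**Conclusion.** The point holds: as stated, the element contrast does not isolate an element. Under the plan's 50% assumption, the inherited part is 0.5 / (1 − p) of the any-support difference when all element-unexposed parents are the reference, which is 56% to 83% for p from 10% to 40%. It is 100% when parents without any intervention are the reference and are taken to be the unsupported half. The SD figures depend on the assumed 0.27 SD and the assumed prevalences, and they are before adjustment.

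A reader might conclude that every inert element will look effective, or that the second study question cannot be answered. Neither follows. In the illustration an inert element reaches significance in 15% to 61% of studies, well above 5% but far from always. The study question asks for associations, which can be estimated. What the stated contrast cannot support is the Discussion's claim to show which elements are effective.

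**What to change.** 1. For element analyses, either restrict to parents who received support and compare those with and without the element, or keep all parents and add an any-parenting-support indicator beside the element term. Define that indicator explicitly, including whether routine visits and informal sources count. The questionnaires and electronic files already planned supply the data.
2. For elements coded from the intervention manual, account for clustering by intervention (random intercept or cluster-robust standard errors). The article considers clustering by organisation only.
3. Report elements that always occur together as one bundle.
4. Keep supported versus unsupported for the overall question, and state that the 0.27 SD detectable difference applies only to that contrast.
5. Word element results as associations.

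The change is to analysis wording and modelling, with no new data. The cost is precision: roughly 0.39 SD detectable at a 150/150 split, rising to 0.65 SD at 30/270. The latter exceeds the 0.5 SD that the plan calls meaningful. These figures use the organisation-level design effect and all 300 supported parents. Clustering by intervention, for which no intra-class correlation is given, or excluding support that cannot be coded, would change them. Confounding by indication for a particular intervention, and by elements that partly co-occur, would remain.
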